## BACKGROUND

Colorectal cancer (CRC) screening, early detection and improved treatment have led to rising survival rates over the past decades. This improvement has resulted in an increasing number of long-term CRC survivors with no residual disease. Most survivors manage to establish a 'new normal' after finishing treatment, but some survivors experience difficulties in normal functioning and decreased quality of life (QoL) due to substantial psychological strain. One of the most common concerns among cancer survivors is fear of cancer recurrence (FCR)[1], defined as "*Fear, worry or concern relating to the possibility that cancer will come back or progress*[2]". The severity of self-reported FCR does not seem to differ much between different cancer types[3] and FCR can persist among very long term survivors[4]. Higher FCR is associated with several psychological factors including (health) anxiety[5], depression[6], perceived uncertainty in illness, perceived risk of recurrence and negative beliefs about worry[7, 8]. Clinically significant FCR (i.e. clinical FCR) is thought to be characterized by "*A preoccupation with the cancer returning or progressing, unhelpful coping behaviors, impairment to daily function, clinically significant distress and limited capacity for making future plans*[2]".

Most CRC survivors report some degree of FCR [9-12]. Two recent studies report likely clinically significant FCR among 13,7 % [13] and 10,1 % [14] of CRC survivors (unpublished data, personal communication) based on a validated measurement questionnaire (Fear of Cancer Recurrence Inventory, FCRI). Despite this the prevalence of clinical FCR in CRC survivors is still somewhat uncertain, as estimates are based on studies with small samples [n=51-91][10, 11, 13, 14], or studies with simple[9, 12] or unvalidated[11] FCR measures.

Two large cohort studies focusing on patient reported health-related quality of life after (colorectal) cancer do exist. The English study [15-17] includes people "living with and beyond cancer", which does not distinguish between survivors with no residual disease, with cancer still present, or with a history of recurrence and furthermore FCR is assessed by a single item. The Dutch PROFILES registry [3] includes no proposed cut-off score for clinical FCR.

A diagnosis of cancer is life changing and imposes heavy stress on patient and relatives. Together with often numerous physical symptoms and social changes after the cancer treatment, the net sum of stressors may exceed the cancer survivor's ability to adapt. This overload may manifest as a functional disorder/somatic symptom disorder such as bodily distress syndrome or health anxiety, as proposed by Simonelli et al [18]. Bodily distress syndrome is defined as a condition in which the patient suffers from, usually multiple, bodily symptoms in a characteristic symptom and illness pattern that are not attributable to verifiable, conventionally defined diseases [19].

Health anxiety is characterized by preoccupation with fear of having a serious and life-threatening illness with no objective sign of disease, and preoccupation persists despite medical reassurance [20]. Health anxiety and FCR obviously overlaps, as they also both include unpleasant thoughts or ruminations, which interfere with everyday life and may lead to further unnecessary investigations and treatment. One study investigated hypochondriasis (the cousin of health anxiety) in breast cancer survivors and found that 43 % of those with clinical level of FCR met the diagnostic criteria [21]. Two studies of CRC patients have measured somatization, but not FCR [22, 23]. To the best of our knowledge, no previous studies have investigated the role of functional disorders in relation to FCR, anxiety and depression in CRC survivors.

Illness uncertainty has been linked with FCR [7] and health anxiety [24]. Illness uncertainty might be even greater when diagnosed asymptomatic as a consequence of screening. We postulate that screened to diagnosis leads to increased issues in coping with the cancer and the fear of recurrence. The comprehensive Danish Clinical Registries contain data on the method of diagnosis, e.g. if the CRC survivor is identified through the Danish Nation-wide Colorectal Cancer Screening Program, as opposed to a survivor initially diagnosed as a result of symptoms. This enables research in this unexplored area of psychosocial consequences of screen-detected cancers.

Around one fourth (26,5 %) of CRC survivors[16] and 20-56 % of people living with and beyond CRC cancer[25] report psychosocial assistance in coping with FCR to be an important unmet need. Randomized controlled trials testing interventions for reducing FCR have primarily been conducted in breast cancer survivors or mixed cancer populations. Most interventions are based on variations of cognitive-behavioral therapy (CBT). The delivery format of interventions previously or currently being evaluated has been in groups[26-28], face-to-face[29-31], blended[32], by telephone[33, 34] or by web-based platforms[35-37].

“ConquerFear” [29] is an individual face-to-face therapist-delivered intervention with demonstrated efficacy in reducing FCR versus a relaxation training attention control group in a mixed cancer sample of whom the majority (89%) were women with breast cancer. As this is a resource- and time-consuming approach accessible primarily to those in close proximity to major metropolitan cancer centres with highly trained psychologists, a web-based self-management version of ConquerFear has been created (iConquerFear), similar in curriculum content, but different in delivery.

Web-based interventions have the potential to fill an important gap in quality cancer care by augmenting limited available mental health services[38]. Web-based therapist-guided cognitive therapy has advantages for both patients and providers and effects appear comparable to traditional face-to-face therapy in treating distress in patients with cancer[39, 40]. Evidence suggests that guided interventions may be superior to unguided interventions [41].

## AIM

The primary aim of this randomized controlled trial (RCT) is to test if a therapist-guided version of iConquerFear (TG-iConquerFear) can reduce FCR and improve QoL for CRC survivors more than augmented treatment as usual (augmented TAU).

Secondary objectives are to i) outline the prevalence of FCR in a population based CRC cohort up to 5 years post-diagnosis using a validated FCR measure with a clinical cut-off. This comprehensive screening will be used as recruitment for the RCT; ii) Investigate whether being diagnosed as a consequence of the Danish Nation-wide Colorectal Cancer Screening Program increases FCR compared to being diagnosed as a consequence of physical symptoms; and iii) investigate whether FCR is associated with anxiety, depression, bodily distress syndrome and health anxiety in CRC survivors as well as investigate whether uncertainty in illness, negative beliefs about worry and perceived risk of cancer recurrence act as moderators or mediators of FCR.

## METHODS/DESIGN

### Study design

#### Survey

This study is a population based cross sectional study. Participants will be invited to answer an electronic questionnaire to screen for fear of cancer recurrence and other psychological factors. The survey will be send out between September 2020 and September 2022.

#### RCT

This study is a population based randomized controlled clinical superiority trial. Participants are randomized to internet-based, TG-iConquerFear or augmented TAU (1:1), see Fig. 1. All participants will follow the standard cancer follow-up program.

Fig. 1, Trial design

[figure not shown]

### Study population

All Danish CRC survivors above age 18 diagnosed after implementation of the CRC screening programme in March 2014 who have completed curative-intent cancer treatment with surgery and/or radiation and/or adjuvant chemotherapy will be invited to participate in the survey. Estimated number is 15,000 as the incidence is 5,000, and 80 % are offered curative intent treatment. One-year survival rate (data from 2011-2015) is 85 %. 5-year survival rate is 65 %. Overall survival rate used for this estimation is 75 %.

The RCT participants are recruited among the 15,000 colorectal cancer survivors invited to take part in survey. Through cooperation with the Danish Cancer Society we expect a slightly higher response rate than previous reported [43] of 60 %.

Among those 9,000, 12 % (1,080) are expected to score 22 or above on the FCRI-SF [13].

Approximately half of those are expected to be willing to participate in a randomised trial[37], resulting in 540 eligible participants.

The survivors will be identified through the Danish Colorectal Cancer Group (DCCG) database hosted by The Danish Clinical Registries (RKKP) with no need to enter individual patient records. The registry does not contain data on recurrence, and the cover letter will need to explain carefully, that in case of disease recurrence, the participants are asked to notify us in the first question or simply ignore the inquiry from us (see appendix 2. Følgebrev).

### Inclusion criteria for participating in the RCT:

- Completed curative-intent cancer colorectal treatment with surgery and/or radiation and/or adjuvant chemotherapy between 01.03.14 and 31.12.18
- No history of recurrence after primary operation
- Fear of Cancer Recurrence Inventory score at or above 22
- Age above 18
- Read and understand Danish
- Access and ability to use Internet

### Exclusion criteria for participating in the RCT:

- Severe psychiatric or cognitive disorder identified during telephone interview

- Cancer recurrence at any follow-up
- Substance abuse

## Procedure

### Part 1, survey

The CRC survivors will be invited by mail to their secure, personal electronic box (E-boks) to electronically fill out the 63-item screening questionnaire comprising: The FCRI-short form (FCRI-SF) assessing FCR severity, bodily distress symptoms (BDS checklist), health anxiety (Whiteley-8), anxiety (SCL4-anx), depression (SCL6-dep), and two items assessing global overall health and global quality of life (Visual Analogue Scale (VAS) 0-100). Two items asks for time since last cancer surveillance visit at the hospital and time until next visit. Participants are asked to answer yes or no regarding received chemotherapy or radiation. One item asks for consent to answers being used for research in anonymous form. Questionnaires and supplemental questions are listed in appendix 6 (Spørgeskemaer).

Completed questionnaires will be exported directly into the RedCap database for clinical research. Those with no access to Internet will be invited by paper and the data will be manually entered in RedCap. In case of no response, a reminder will be send after 2 weeks. All participants will be informed of their current level of FCR based on their answers.

### Part 2, recruitment

In cases where participants in Part 1 report a FCRI-SF score  $\geq 22$  indicating likely clinically significant FCR [44], they will automatically be asked if they want to hear more about an experimental intervention targeting FCR, and 12 more questions appears on uncertainty in illness, negative beliefs about worry and perceived risk of cancer recurrence along with the full version of the FCRI (appendix 6). See Fig. 2 for timeline[45].

All survivors with likely clinically significant FCR who agree to be contacted by a research assistant (primary investigator or one of the two psychologists who will perform the intervention. All has been sufficient trained) will be telephoned, informed orally about the RCT and interviewed using the mini-SCAN, a brief semi-structured interview for psychiatric diagnosis [46]. This interview is designed to ensure appropriate treatment is offered to prospective study participants. If information and miniSCAN cannot be performed at the same time, a new appointment will be made. In case of severe depression or severe psychiatric or cognitive disorder, the survivor will be excluded from the study and encouraged to seek relevant help through their general practitioner. When needed, the research assistant can consult a psychiatrist. Supervision will be performed on regular basis.

The contacting research assistant will declare oral information given (appendix 4. Erklæring om videregivelse af mundtlig information) and for potential participants meeting eligibility criteria initiate for RedCap to send out written participant information sheet (appendix 3.

Deltagerinformation) and consent form (appendix 5. Samtykkeerklæring til projektdeltagelse) to the participant's E-boks. By entering their Nem-id (a Danish secure personal coding system for electronic movements) they will consent to participation and concealed, computerized variable block randomization (1:1) stratified for age and gender will happen immediately.

Fig. 2, Timeline

|                          | STUDY PERIOD         |           |               |              |                 |           |
|--------------------------|----------------------|-----------|---------------|--------------|-----------------|-----------|
|                          | Population Screening | Enrolment | Randomization | Intervention | Follow-up       | Close-out |
| TIMEPOINT                | $-t_2$               | $-t_1$    | $t_r$         | $t_i$        | $t_0, t_1, t_2$ | $T_3$     |
| ENROLMENT         |                      | X         |               |              |                 |           |
| Screening                | X                    |           |               |              |                 |           |
| Semistructured interview |                      | X         |               |              |                 |           |
| Informed consent         | X                    | X         |               |              |                 |           |
| Randomization            |                      |           | X             |              |                 |           |
| INTERVENTIONS     |                      |           |               |              |                 |           |
| TG-iConquerFear   |                      |           |               | X            |                 |           |
| Augmented TAU     |                      |           |               | X            |                 |           |
| ASSESSMENTS       |                      |           |               |              |                 |           |
| FCRI-SF           | X                    |           |               | X            |                 |           |
| Recurrence        | X                    |           |               |              |                 |           |
| Supplementary     | X                    |           |               |              |                 |           |
| Full FCRI         |                      | X         |               |              | X               | X         |
| SCLs              | X                    |           |               |              | X               | X         |
| BDS               | X                    |           |               |              | X               | X         |
| Whiteley-8        | X                    |           |               |              | X               | X         |
| QoL               | X                    |           |               |              | X               | X         |
| MUIS              |                      | X         |               | X + X        | X               | X         |
| MCQ-30            |                      | X         |               | X + X        | X               | X         |
| Perceived risk    |                      | X         |               | X + X        | X               | X         |

**Part 2 b, randomization**

*If randomized to augmented TAU:* The control group is described as “augmented” as the diagnostic telephone interview exceeds standard treatment. Furthermore, if randomized to augmented TAU the information letter (appendix 7. Informationsbrev) send to E-boks will include a reference to a website with a non-guided, publicly available E-learning program in cancer rehabilitation hosted by the Region of Central Jutland (livogkraeft.rm.dk). The website includes, besides a written material, self-help instructions for meditation. Use of the website will not be monitored.

*If randomized to TG-iConquerFear:* The information letter (Appendix 7. Informationsbrev) will contain a link to enter the platform directly. The assigned therapist will be informed simultaneously.

Both groups will follow standard surveillance according to national guidelines for cancer recurrence at a surgical or oncological department, which may include colonoscopy and/or CT scans. The municipality is responsible for rehabilitation and offers limited access to physical exercise, yoga, dieticians, psychologists, sexologists etc.

### **Part 3, pilot study**

The first 20 CRC survivors will be evaluated separately as a pilot group to explore barriers and facilitators for entering and completing internet-based therapy. Furthermore, we will optimize the feasibility of TG-iConquerFear in a small population before launching a comprehensive RCT. To ensure continuity between screening, recruitment, and the RCT no questionnaires will be sent out while we evaluate the pilot study. If the pilot study does not raise any need for major changes in the study design or procedures, the pilot study will seamlessly proceed to the RCT.

### **Part 4, intervention**

The theoretical frame of iConquerFear[29] is based on the Common-Sense Model (CSM) of illness, the Self-Regulatory Executive Function model (S-REF; targets metacognitions) and Relational Frame Theory (RFT; theoretical basis for Acceptance and Commitment Therapy). The intervention includes elements of attention training, increasing metacognitive awareness, acceptance & mindfulness, promotion of expedient screening behaviour, and values-based goal setting. The platform is accessed through secure log-on and comprises 5 modules containing educational text, interactive exercises, short videos featuring doctors, therapists and patients' perspectives, see Fig. 3.

The Australian version of iConquerFear is completely self-directed.

The Danish version of iConquerFear will contain a messenger-function on the intervention dashboard, allowing the participant and therapist to communicate asynchronously (TG-iConquerFear). The participant is guided through the sessions by minimum weekly contact with an experienced therapist. The therapist will motivate, answer questions and give feedback on written material and exercises. The amount of contact will be recorded and explored as a moderator of intervention efficacy. Should any cancer-related questions occur, an oncologist or surgeon will be involved as a consultant to the therapists.

The programme can monitor adherence, dropouts and track log-ins and activity. A purpose-developed single-item questionnaire within the TG-iConquerFear will each week ask for level of engagement[47]. Participants who do not adhere to, or withdraw from, the intervention will be contacted by telephone and asked why. These participants will be asked if they would be willing to complete a post-intervention assessment and all follow-up assessments to aid intervention evaluation. Therapist assistance is scheduled to last 10 weeks, but the participants will have free access to the platform for another 6 months.

In case of recurrence during the 10 weeks of intervention, the participant will be excluded from analysis, but may continue in the programme.

Fig. 3, iConquerFear curriculum content

| Module                                                                                                                                              | Content and Features                                                                                                                                                                                                                                                                                                                                                        |
|-----------------------------------------------------------------------------------------------------------------------------------------------------|-----------------------------------------------------------------------------------------------------------------------------------------------------------------------------------------------------------------------------------------------------------------------------------------------------------------------------------------------------------------------------|
| 1. Introduction and orientation                                                                                                                     | 
 
• Introduction to FCR (survivor videos)
 
• Overview of FCR treatment model (interactive animation and therapist video)
 
• Values clarification (interactive card sort exercise)
 
                                                                                                                           |
| 2. Attention training                                                                                                                               | 
 
• Introduction to Attention Training (Interactive, therapist video, Attention Training audio, monitoring and feedback, regular practice reminders)
 
                                                                                                                                                                        |
| 3. Detached mindfulness                                                                                                                             | 
 
• Introduction to Detached Mindfulness (Therapist videos)
 
• Demonstration of Detached Mindfulness exercises (Animated videos, therapist feedback)
 
                                                                                                                                                                |
| 4. Learning to live well and manage worry                                                                                                           | 
 
• Psycho-education regarding appropriate threat monitoring behaviours (Annotated PowerPoint video)
 
• Assessing compliance with follow-up & self-examination recommendations (Interactive exercise with personalised feedback)
 
• Worry management techniques (Textual overview and downloadable PDF)
 
 |
| 5. Treatment summary and relapse prevention                                                                                                         | 
 
• Assessment and feedback on change in FCR symptoms during treatment (therapist feedback)
 
• Consolidation of newly acquired strategies for managing FCR through relapse prevention (therapist feedback and downloadable action plan)
 
                                                                             |
| Features common across all modules include: Write to your therapist, interactive exercises, downloadable handouts, progress graphs and safety plan. |                                                                                                                                                                                                                                                                                                                                                                             |

The design of the RCT and the procedure of delivering oral and written information and consenting by Nem-id is inspired by and has proven feasible in the protocol “A randomised controlled trial of Internet-based acceptance and commitment therapy (iACT) to patients with health anxiety” approved by the Regional Committee on Health Research Ethics for Central Jutland the 23rd November 2015, reference number ESDH 1-10-72-321-15. The process of participation is further elaborated below:

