### Process of participation

1. Receives “Følgebrev” and a survey (Spørgeskemaer, bilag 1 – screening) in E-boks.
2. Answers. Or reminded after 2 weeks
3. In case of FCRI under 22: No further participation
4. In case of FCRI at or above 22:
  - Informed of elevated level directly in the questionnaire
  - Asked if interested in hearing more about the RCT targeting FCR
  - Asked to enter phone number
  - Asked to fill out another questionnaire (45 items)
5. Telephoned by a research assistant, oral information about RCT is given (purpose, risks, benefits, voluntariness). Rescheduling in case of needing assessor.

6. Semistructured interview is performed by telephone. If possible at the same time as oral information is given, otherwise rescheduled.
7. In case of eligibility and wish to participate: Written information about RCT "Deltagerinformation", consent form "Samtykkeerklæring til projektdeltagelse" and "Før du beslutter dig"-pamphlet is send to E-boks
8. Consenting with Nem-id. Or reminded after 2 weeks of consideration.
9. No answer in 4 weeks is interpreted as not wanting to participate.
10. If consent is given: Randomization
11. Information letter "Informationsbrev" to E-boks, either with link to livogkraeft.rm.dk (control arm) or link to TG-iConquerFear (intervention arm)
12. Control arm or intervention arm for 10 weeks (Spørgeskemaer, bilag 3 – mediationsparametre)
13. 12 weeks after consent form is signed: 1st follow-up (Spørgeskemaer, bilag 4 – follow-up)
14. 12 weeks after 1st follow-up: 2nd follow-up
15. 12 weeks after 2nd follow-up: 3rd follow-up
16. 24 weeks after 3rd follow-up (One year after consent form is signed): 4th and final follow-up

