## EVALUATION

### Primary outcome measure

The primary outcome measure is the 3 month follow-up (T1) total score on the recently validated Danish version of the FCRI [13]. The FCRI is a 42-item self-report measure that includes subscales assessing FCR triggers, severity, psychological distress, functioning impairments, insight, reassurance, and coping strategies [48]. The FCRI has demonstrated high: internal consistency ( $\alpha=0.96$ ) [49], interclass correlation (0.84) [13] and convergent validity in large heterogeneous cancer survivor samples. Respondents rate the degree to which symptoms/issues affected them over the past month on a Likert scale ranging from 0 ('not at all' or 'never') to 4 ('a great deal' or 'all the time'). While there are potential issues with aggregating FCRI subscales [50], total FCRI score will be used as the dependent variable, as it closely reflects proposed features of clinically significant FCR; namely related distress, functional impact, and maladaptive coping[2], rather than the level of fear indicated by the FCRI-SF [50, 51]. Total scores can range from 0-168; higher scores indicate greater FCR morbidity. Level of FCR will be measured post-treatment (T0) and at follow-up after 3 (T1) and 6 (T2) months. Long-term effect will be evaluated after one year (T3). All electronic questionnaires will be sent out automatically through RedCAP.

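### The only personal request for follow-up data described after randomisation is tied to stopping the intervention, so recovery of the primary outcome can differ by arm

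*Combined protocol and SAP*

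**What the plan says.** **Intervention arm.** Protocol, Part 4 (intervention): "Participants who do not adhere to, or withdraw from, the intervention will be contacted by telephone and asked why". It continues: "These participants will be asked if they would be willing to complete a post-intervention assessment and all follow-up assessments to aid intervention evaluation". Non-adherence is visible because "The programme can monitor adherence, dropouts and track log-ins and activity".

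**Control arm.** Protocol, Part 2 b (randomization), on the e-learning site offered to controls: "Use of the website will not be monitored".

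**Both arms.** Protocol, Primary outcome measure: "All electronic questionnaires will be sent out automatically through RedCAP". No chasing of unanswered follow-up questionnaires is described. The reminders that are described come before randomisation. One is at the screening survey (Part 1): "In case of no response, a reminder will be send after 2 weeks". The other is at the consent step (Process of participation, step 8): "Consenting with Nem-id. Or reminded after 2 weeks of consideration".

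**Analysis.** SAP section 3 makes the intention-to-treat set primary. Section 5.2 tests the between-group difference in mean change with a two-sample t-test, or a non-parametric equivalent. Section 6 plans no imputation. Linear mixed models across baseline and follow-up are secondary (section 5.3).

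**The concern.** The stated trigger for personal contact is an event that only one arm can show. A control participant has no monitored programme to stop, and so cannot set off the call. An adherent intervention participant who ignores the 3-month questionnaire does not set it off either. As written, an intervention participant who disengages is asked in person for the primary outcome, while a control participant who goes silent gets an automatic questionnaire and nothing further that the text describes.

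This matters because the primary test uses observed cases, despite its intention-to-treat label. If the call brings in people whose course differs from that of the other responders, their scores enter the intervention mean, while comparable people in the control arm stay missing. The comparison is then between two differently selected groups of responders.

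**Working it through.** The documents give no figure for outcome recovery by arm, so there is nothing of the plan's to reproduce. The check has two parts.

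**1. Is there a control-arm equivalent?** After randomisation, the text has:

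| Step | Intervention arm | Control arm |
|---|---|---|
| Automatic questionnaires | Yes | Yes |
| Monitoring of use | Yes, by the platform | No |
| Call after stopping | Yes | None described |
| Request in person for follow-up data | Yes, in that call | None described |
| Reminder or call after a missed FCRI | None described | None described |

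The asymmetry is in the text. The trigger is adherence, not a missing outcome.

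**2. How large could the effect be?** Every input below is an assumption except the planning values of d = 0.5, difference 3.5 and SD 7 (protocol, Power calculation). The range for f is taken from the planned dropout of 30% (protocol and SAP section 2) and 20% (SAP update of September 2023).

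- f = share in each arm whose 3-month score would otherwise be missing: 0.20 to 0.30
- g = how much worse their change is than that of responders: 0.25 to 0.50 SD
- r_I, r_C = share of them recovered in each arm: 0.30 to 0.50 and 0

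With f and g equal in both arms and no true effect, the shift in the observed-case difference (intervention minus control, positive = intervention looks worse) is

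f·r_I·g / (1 − f + f·r_I) − f·r_C·g / (1 − f + f·r_C).

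With r_C = 0 the second term is zero:

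| f | g | r_I | Shift (SD) | Points at SD 7 | Completeness, intervention vs control |
|---|---|---|---|---|---|
| 0.20 | 0.25 | 0.30 | 0.015/0.86 = 0.017 | 0.12 | 86% vs 80% |
| 0.20 | 0.25 | 0.50 | 0.025/0.90 = 0.028 | 0.19 | 90% vs 80% |
| 0.20 | 0.50 | 0.50 | 0.050/0.90 = 0.056 | 0.39 | 90% vs 80% |
| 0.30 | 0.25 | 0.50 | 0.0375/0.85 = 0.044 | 0.31 | 85% vs 70% |
| 0.30 | 0.50 | 0.30 | 0.045/0.79 = 0.057 | 0.40 | 79% vs 70% |
| 0.30 | 0.50 | 0.50 | 0.075/0.85 = 0.088 | 0.62 | 85% vs 70% |

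The range is 0.02 to 0.09 SD. Against d = 0.5 that is 0.017/0.5 = 3% to 0.088/0.5 = 18%. If recovery is equal, for example r_I = r_C = 0.50, the two terms cancel and the shift is 0. If recovered participants do better than responders, g changes sign and so does the shift.

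**Upper limit.** Calls alone create a completeness gap of f·r_I. A gap of 20 percentage points would need r_I = 0.20/0.20 = 100% at f = 0.20, or 0.20/0.30 = 67% at f = 0.30, with nobody recovered among controls. That is too much to expect of a call that reaches only non-adherers, some of whom would have answered the automatic questionnaire anyway.

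**The case against.** The strongest reply is that the call answers a cause of loss that exists in one arm only. Only TG-iConquerFear has a 10-week guided programme to abandon, and asking people who stop treatment to stay in follow-up is what an intention-to-treat analysis needs. The call may therefore narrow a gap. If, say, 30% would be missing in the intervention arm and 20% among controls (assumed), recovering one third of the former equalises completeness: 0.70 + 0.30/3 = 0.80. This stands, and it is why the call should be kept and no direction claimed.

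Second, silence is not proof of absence: the information letters and questionnaires are in appendices outside this text. This also stands, so the claim is only that no equivalent is described.

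Third, the analysis is not without protection. The mixed models in SAP section 5.3 use partial follow-up and are valid if data are missing at random. The protocol's Dropout analysis says that differences between participants and dropouts will be allowed for later, but names no method. This stands in part: the models are secondary, and they do not cover outcomes missing because of the unobserved score. So a reader who infers that the problem is beyond any analysis goes too far.

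Two other stronger readings are not supported:

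- **That the call is itself a material co-intervention.** The intervention arm already has at least weekly therapist contact by design, and one call adds little to that.
- **That the calls did raise completeness in the intervention arm.** The SAP update of January 2025 reports that the five passive users gave no outcome data. That does not repair the plan, but the documents offer no evidence that recovered non-adherers entered the intervention mean.

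**Conclusion.** The point holds as a statement about the planned procedure. The one described personal request for follow-up data after randomisation can be set off only in the intervention arm, and the observed-case primary test passes any resulting difference in recovery into the estimate.

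The direction is unknown. If recovered non-adherers do worse than responders, the shift runs against the intervention, so a reader should not infer that the arrangement favours TG-iConquerFear. The size is probably modest: about 0.02 to 0.09 SD, or 0.1 to 0.6 points if the planning SD of 7 applies, against a planned 3.5. These figures rest on assumed missingness, prognostic gap and recovery shares, equal in both arms before any call. The conclusion also depends on the unseen appendices containing no reminder or call for missed follow-up questionnaires.

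**What to change.** Leave the Part 4 call as it is, including its timing: asking promptly why people stop serves the pilot's aim of exploring barriers. Add one retention procedure to the protocol for every randomised participant:

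- **Trigger:** an unreturned FCRI at T0 or T1, in either arm.
- **Steps:** the same automatic reminder, then one scripted call at a fixed interval.
- **Caller:** a research assistant who is not the participant's therapist.
- **Request:** the FCRI first, the other scales only if the participant is willing.
- **Record:** how each outcome was obtained (automatic, after the reminder, after a call), by arm.

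The existing call will still reach some intervention participants earlier, so effort will not be perfectly equal. The record shows how much of a difference remains.

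The cost is protocol wording, a REDCap alert and about 68 × 0.20 = 13.6, so roughly 14 calls per visit across both arms at the revised sample size and dropout. Research assistants are already trained for telephone contact. No sample size figure changes.

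The January 2025 update suggests that data collection may have closed. In that case, report T1 completeness by arm, flag outcomes obtained after a call, and add a missing-not-at-random sensitivity analysis. That analysis should shift the missing T1 scores separately in each arm, over a range that includes 0 to 0.5 SD, and state where the conclusion would change.
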